### Recruitment

#### Recruitment of Schools

Six post-primary schools were recruited in Northern Ireland and six in Bogotá during 2019. In Northern Ireland, schools were selected to ensure a mix of State and Catholic maintained schools, with some serving urban and rural catchments, and maximum variation sampling to ensure schools with high and low proportions of pupils eligible for free school meals. In Bogotá, six public schools from low to middle socio-economic status with maximum variation by geographic location were selected.

In Northern Ireland, relevant schools were identified from the database of schools which have previously been involved in research with the Center for Public Health and School of Education (currently over 200 schools in Northern Ireland). Schools were selected based on the sampling framework highlighted above. Schools identified as eligible were sent a letter (addressed to the school Principal or relevant senior member of staff) outlining the purpose of the study and inviting them to take part. A follow-up phone call by a member of the research team, ~1 week after delivery of the invitation letter, provided further details and an opportunity to answer any questions. For those schools agreeing to take part, a study pack was delivered providing further details about the study and role of the school.

In Bogotá, the sampling of schools followed these steps. First, a list of 40 private and public schools were prioritized based on health risks by the Education and Health Departments of Bogotá. Second, from this list, 13 schools were invited to participate according to the following inclusion criteria: (1) schools in an urban area; (2) including boys and girls; (3) having an enrollment of between 90 and 150 students in 7th year. Third, only six schools accepted the invitation and were selected for the final sample. These schools were assigned randomly to each of the interventions. Three schools were assigned to the ASSIST (*Entre Parceros*) intervention, and the other three were assigned to the Dead Cool (*Bacan*í*simo*) intervention. Schools identified as eligible were visited multiple times and researchers presented the outline of the study to the school Principal and to relevant members of staff, and invited them to take part. For those schools agreeing to take part, a study pack was delivered providing further details about the study and role of the school.

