##### Measuring injunctive social norms related to smoking

To measure injunctive norms about smoking behavior (i.e., beliefs about the appropriateness of smoking and vaping related actions), we used another Coordination Game. The actions evaluated in this game include: (i) a parent smoking in their own home in front of their children who are under the age of five; (ii) an adult smoking in a car with children under the age of 16 in the car; (iii) someone selling cigarettes to a teenager who looks younger than 16 without requesting proof of age; (iv) a lead actor seen smoking in the opening scene of a recent superhero movie; (v) an older school pupil smoking outside school (e.g., at a bus-stop); (vi) a school pupil using an e-cigarette while walking to school; (vii) a pupil sharing a photo of himself/herself using an e-cigarette on social media (e.g., Facebook, Instagram); (viii) a school pupil using chewing tobacco. We adapted the Krupka and Weber (17) protocol to elicit beliefs about the injunctive norm by asking participants to coordinate with their year group peers in estimating the social appropriateness of various smoking related behaviors on a six point Likert scale that ranges over “extremely socially inappropriate” to “extremely socially appropriate” (i.e., as above their pay-off in the choice task is determined by whether their response matches the most common response given by the year group). By undertaking this Coordination game both pre- and post-intervention, we can identify whether or not some of the target norms (e.g., attitudes related to peer smoking) have changed, while acknowledging that injunctive norms for other behaviors [defining and identifying social norms unrelated to smoking] are not anticipated to be affected by the prevention programs (negative controls). This allows us to create one type of metric with which to understand the effects of the interventions on classroom social norms.

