### Statistical Methods

#### Elicitation of Social Norms and Social Network Analyses

Injunctive social norms will be modeled quantitatively, such that a decision maker's “pay-off” u(a_k_) from a set of actions V {π(a_k_)} is related to the parameter γ ≥ 0, representing the degree to which the individual cares about adhering to social norms, in: u(a_k_) = V {π(a_k_)} + γN(a_k_), with the function N capturing the social norm, [i.e., the social appropriateness of action a_k_ denoted by N(a_k_)]. We let N_g_(a_k_) denote the social norms for group *g*, estimated from the Coordination games. γ is the key parameter reflecting individual sensitivity to the norm, estimated using the total number of balls allocated to the blue “rule following” bucket in the RF task. The Dictator and Coordination games allow us to identify norms related to prosocial behavior and to smoking related activities in the target population. We can then explore whether the norms related to smoking actually do change and whether data from the RF experiments help us predict who is more sensitive to following those changed norms after the intervention. We will also measure correlations (Spearman's rank correlation) between an individual's norms-sensitivity parameter and his/her decisions in the Donation game. We will use tobit regressions that allow for censoring, regressing the distance (Δ_SNdist_) between an individual's choice and the observed average norm (average Dictator choice) in the relevant reference group on his/her norm-sensitivity parameter. The tobit regression allows us to see if there is a statistically significant relationship between norm-sensitivity and the changed norms after the intervention. We will use similar techniques when examining social norms related to tobacco use and individuals' abilities to identify them in the Coordination game. For each behavioral vignette (whose appropriateness is rated), we will calculate a correlation between individuals' norms-sensitivity parameters, and their chosen score on the social appropriateness scale, after calculating (Δ_SNdist_). Scores on the appropriateness scale are categorical, requiring ordered probit regressions. We will conduct the above analysis both pre- and post-intervention but since we will have two observations for each individual, we will use the respective panel random effects versions (including a dummy variable to identify post-intervention observations). In all regressions, we will calculate standard errors clustered on school classes. We will account for individual participants' demographic and psychosocial characteristics, and dummy variables signifying intervention type (ASSIST or Dead Cool intervention) and country (Colombia or Northern Ireland).

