${\text{H}}_{0}^{3}$**: that social norms at the class and year group level are independent of social network structure**: a novel aspect of this proposal is that we will examine how social norms sensitivities (Δ_SNdist_) cluster among friendship groups (before and after the two interventions), and thus examine possible mediating mechanisms for the intervention effects and whether they are moderated by social network structure. We will extend the clustering method presented by Grimmer and King (70), using a Markov Chain Monte Carlo (MCMC) model to integrate various attributes of the students and their social norms sensitivity parameters in the first step of the *a posteriori* clustering selection framework. Examining the influence of individual student attributes (their norms sensitivities; psychosocial traits like self-efficacy, and the number of family members who smoke) within a MCMC framework permits inference based on well-known expectation and maximization algorithms. We note that peer influence was inferred using hidden Markov models (7) applied to *before* and *after* data from three ASSIST schools, but with a similar per country sample size as Steglich et al. (7), we will obtain superior experimental measures of norms and thus populate the MCMC models with real rather than inferred parameters. If homophily is not stable over one semester, in a sensitivity analysis we will use an instrumental variable approach, instrumenting on orthogonal characteristics of students not nominated by the ego but who were friends of their friends, using characteristics that should not plausibly predict the egos' norms sensitivity (Δ_SNdist_), nor friendship structure (71).

${\text{H}}_{0}^{4}$**: that the changes in smoking related norms are the same in schools which were offered the ASSIST intervention and in those which were offered the Dead Cool intervention**: we will use a regression based approach permitting adjustment for the multilevel clustered nature of the data, comparing the change in smoking related norms (identified through the Coordination games) in ASSIST and Dead Cool Schools and between UK and Colombian Schools.

${\text{H}}_{0}^{5}$**: that any changes in social norms are independent among members of the same friendship clique**: see section sample size.

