#### Mediation Analyses

The relationship between intervention (ASSIST vs. Dead Cool) and smoking related norms (${\text{H}}_{0}^{4}$) will be examined for mediation by the psychosocial traits (i.e., mediators) using the “Cross-lagged panel model for a half-longitudinal design” described by Preacher (72). In each model, a variable indicating intervention group (i.e., ASSIST vs. Dead Cool) will be modeled as a predictor of the mediator at time 2 (i.e., intervention-end); the mediator at time 1 (i.e., baseline) will be modeled as a predictor of the mediator at time 2 and smoking related norms at time 2; smoking related norms at time 1 will be modeled as a predictor of smoking related norms at time 2. Time 1 variables will be permitted to covary (72). The significance of indirect effects will be assessed using the structural equation modeling (SEM)-based product-of-coefficients approach (73) with 95% confidence intervals (CIs) estimated using the bias-corrected bootstrap (with 10,000 iterations) procedure (74, 75). Model fit will be assessed using recommended indices and cut-points (76). These analyses will be repeated to examine the relationship between mediators and smoking behavior/intentions.

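### The H4 comparison of ASSIST with Dead Cool is set on change in smoking norms and states no adjustment for the pupil's baseline norm score, although that score is collected

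*Protocol article*

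**What the plan says.** All places are in the Protocol article.

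- **Statistical Methods, H4.** The null is that changes in smoking norms are equal under the two interventions. The method reads "we will use a regression based approach permitting adjustment for the multilevel clustered nature of the data", followed by "comparing the change in smoking related norms (identified through the Coordination games) in ASSIST and Dead Cool Schools and between UK and Colombian Schools". No baseline norm term is named.
- **Elicitation of Social Norms and Social Network Analyses, general covariates.** "We will account for individual participants' demographic and psychosocial characteristics, and dummy variables signifying intervention type", plus a country dummy. The pupil's baseline Coordination-game score is not listed.
- **Measuring injunctive social norms related to smoking.** The score exists at both waves: "By undertaking this Coordination game both pre- and post-intervention, we can identify whether or not some of the target norms" have changed.
- **Mediation Analyses.** The relationship examined is "The relationship between intervention (ASSIST vs. Dead Cool) and smoking related norms", labelled H4, and here "smoking related norms at time 1 will be modeled as a predictor of smoking related norms at time 2".
- **Recruitment of Schools.** For the six Bogotá schools, "These schools were assigned randomly to each of the interventions". No random assignment is described for Northern Ireland.

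**The concern.** Comparing mean change between arms without a baseline term assumes that a pupil who starts one point higher is expected to finish one point higher. When the pre-post correlation is below 1, that over-corrects. If ASSIST schools happen to start with higher scores, regression to the mean makes their change look smaller, so the imbalance enters the contrast with its sign reversed.

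With three schools per intervention in each country, chance imbalance is to be expected. The plan already holds the measurement that would reduce this error, and uses it in the mediation model for the same intervention-to-norms relationship. As written, H4 therefore risks giving up precision, and the article treats baseline norms in two ways without giving a reason.

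**Working it through.** **Inputs from the article.** 100 pupils per school and ICC 0.01 (from the H1 power statement, so borrowed from a different outcome); 3 schools per intervention per country, 6 per intervention overall. **Not in the article:** power, effect size, SD or pre-post correlation for H4. The correlation ρ is an assumption and is shown over a range.

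**The plan's own figures.** Design effect = 1 + 99 × 0.01 = 1.99, as stated. For H1, 600/1.99 = 301.5 effective pupils, which gives 79.6% power for r = 0.16 (stated: 80%). There is no H4 figure to reproduce.

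**Step 1: variance, with one ρ for pupils and schools.** In SD² units, unadjusted change has variance 2(1−ρ) and the baseline-adjusted score has 1−ρ². The ratio is (1+ρ)/2.

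**Step 2: power.** If unadjusted change has 80% power (two-sided 5%), adjusted power is Φ(2.802/√ratio − 1.960). At ρ = 0.5: 2.802/√0.75 = 3.235, and Φ(1.275) = 89.9%.

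| ρ | ratio | adjusted power when change has 80% |
|---|---|---|
| 0.3 | 0.65 | 93.5% |
| 0.5 | 0.75 | 89.9% |
| 0.7 | 0.85 | 86.0% |
| 0.9 | 0.95 | 82.0% |

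**Step 3: chance baseline imbalance.** The SD of the between-arm difference is √(1.99/100 × 2/6) = 0.081 SD for 6 v 6 schools and √(1.99/100 × 2/3) = 0.115 SD for 3 v 3. Unadjusted change carries −(1−ρ) of it. At ρ = 0.5 that is about 0.04 and 0.06 SD.

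**Step 4: different correlations for pupils (ρp) and schools (ρs).** With m = 100 and a pupil-level slope of about ρp, the school-mean variances are:

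- change: 2(1−ρs)·ICC + 2(1−ρp)(1−ICC)/m
- adjusted: (1 − 2ρpρs + ρp²)·ICC + (1−ρp²)(1−ICC)/m

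Take ρp = 0.5 and ρs = 0.9 (both assumed):

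- ICC 0.01: change 0.0020 + 0.0099 = 0.0119; adjusted 0.0035 + 0.0074 = 0.0109; ratio 0.92. Power goes from 80% to about 83%.
- ICC 0.05 (assumed): change 0.0100 + 0.0095 = 0.0195; adjusted 0.0175 + 0.0071 = 0.0246; ratio 1.26. Power falls from 80% to about 70%.

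**Step 5: which baseline term.** School-level t test with an assumed 0.25 SD effect, ICC 0.01 and ρ = 0.5 at both levels:

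| Schools | change | pupil baseline | pupil baseline + school mean |
|---|---|---|---|
| 6 v 6, country in model | 78% | 88% | 83% |
| 3 v 3, one country | 38% | 48% | 34% |

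The school-mean term uses a degree of freedom that so few schools cannot spare.

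**Step 6: fit with the H4 wording.** Change is post minus baseline. Regressing change on arm and baseline gives the same arm coefficient as regressing post on arm and baseline; only the baseline slope shifts, by 1. Adding the covariate therefore does not require abandoning change as the outcome.

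**The case against.** **The article is silent; it does not exclude baseline.** This stands. A reader might infer that the plan rejects baseline adjustment. The text supports only that none is stated, and the covariate detail may sit in a fuller analysis plan. But the article does fix change as the quantity compared and does list covariates, so a request to name the baseline score is fair.

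**Comparing change is defensible in this design.** This stands in part. The study is described as a quasi-experiment and not as a head-to-head comparison, and random assignment is stated only for Bogotá. In non-randomised schools, change and adjusted analyses can answer different questions, and adjustment is not automatically better. Under random assignment, unadjusted change is unbiased over repeated allocations; what it loses is precision.

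**A fixed loss of about 10 points of power.** A reader might take this from the ρ = 0.5 row. The documents do not support it as a property of the plan: it needs an assumed ρ near 0.5 at both levels and 80% starting power. The article also defines norms as collective perceptions, so high school-level stability is plausible, and Step 4 shows that the gain may then be small or negative.

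**A contradiction with the mediation model.** A reader might infer this too. The mediation model is a separate analysis of indirect effects, in which a lagged outcome is a standard part. Its listed paths include no direct path from intervention to time 2 norms, and the article does not propose to split the H4 effect into parts. The two sections handle baseline differently; they do not contradict each other.

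**Conclusion.** The point holds in limited form. H4 compares change in smoking norms and states no adjustment for a baseline score that is already collected and is used elsewhere in the plan.

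Adjustment would usually sharpen the ASSIST v Dead Cool contrast. From 80% power, the gain is about 14 points at ρ = 0.3, 10 at 0.5, 6 at 0.7 and 2 at 0.9. These figures rest on an assumed correlation equal at pupil and school level, and on an ICC borrowed from H1. If school norms are much more stable than individual ratings, the gain shrinks to about 3 points (ICC 0.01) or becomes a loss of about 10 (ICC 0.05).

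No figure stated in the article is invalidated, since H4 carries no power statement. The case is cleanest in Bogotá, where assignment is random and schools are few.

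**What to change.** - **ASSIST v Dead Cool.** State that the planned multilevel regression for H4 includes the pupil's own baseline Coordination-game score and country as covariates. Do not add a school-mean baseline term, because there are few schools.
- **Sensitivity analysis.** Report the unadjusted change comparison beside it, since random assignment is stated only for Bogotá.
- **UK v Colombia.** Keep the change comparison, as country cannot be randomised.

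The cost is a sentence or two of wording and one extra covariate. No new data are needed: a change score already requires both waves. The downside is that in non-randomised schools the adjusted and change estimates may differ, which is why they should be shown together.

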#### Mediation Analyses

The relationship between intervention (ASSIST vs. Dead Cool) and smoking related norms (${\text{H}}_{0}^{4}$) will be examined for mediation by the psychosocial traits (i.e., mediators) using the “Cross-lagged panel model for a half-longitudinal design” described by Preacher (72). In each model, a variable indicating intervention group (i.e., ASSIST vs. Dead Cool) will be modeled as a predictor of the mediator at time 2 (i.e., intervention-end); the mediator at time 1 (i.e., baseline) will be modeled as a predictor of the mediator at time 2 and smoking related norms at time 2; smoking related norms at time 1 will be modeled as a predictor of smoking related norms at time 2. Time 1 variables will be permitted to covary (72). The significance of indirect effects will be assessed using the structural equation modeling (SEM)-based product-of-coefficients approach (73) with 95% confidence intervals (CIs) estimated using the bias-corrected bootstrap (with 10,000 iterations) procedure (74, 75). Model fit will be assessed using recommended indices and cut-points (76). These analyses will be repeated to examine the relationship between mediators and smoking behavior/intentions.

#### Process Evaluation Analyses

In a final qualitative phase, we will evaluate the findings from our quantitative analysis of social norms, and their changes post intervention, by triangulating with data from focus groups with students (one focus group per school with a diverse sample of ~8 students each) and interviews with the designated peer leaders (in the schools receiving the ASSIST intervention) and with teachers (in schools receiving both interventions). Qualitative analysis will draw on the framework approach. Each intervention site will be treated as a “case” and within case analysis conducted by use of framework matrices. A *cross case* comparison will then be made by charting common themes and identifying key mechanisms of action (seeking comparisons across interventions and across countries). Our triangulation approach will first involve sorting of themes; convergence coding (for agreement/partial agreement, silence and dissonance); feedback and interpretative synthesis (77). The overall interpretation of this mixed methods triangulation (and the “proof of concept”) will be tested in a plenary workshop of stakeholders (from public health, education, network science and behavioral economics) using Group Model Building, a participatory approach that is widely used to build the capacity of practitioners to think in a systems way and which employs nominal group techniques to uncover hidden assumptions and build consensus around the possible mechanisms within a complex system (78).

## Discussion

This *proof of concept* study aims to fill a gap in the public health science literature. The research proposed is innovative because it harnesses novel transdisciplinary insights (from Game Theory and Social Network science) about the elicitation and measurement of social norms in order to better understand the effects of school based smoking prevention programs. However, the underpinning methodology will have a wider relevance for the study of other health-related behaviors and for understanding how social norms are mediated by social networks in classrooms and schools. It will provide insights into the psycho-social, cultural, and economic drivers of observed differences in smoking rates among adolescents in high and LMIC settings, producing new knowledge that can help reduce smoking in these settings. It is also significant in aspiring to a deeper understanding of possible mechanisms (through social norms) of *spill-over effects*. Finally, the research is important as it will help build transdisciplinary capacity in public health science in a LMIC setting, with clear pathways to impact. By invoking new approaches from Game Theory and Social Network science, the project will leave a legacy of transdisciplinary skills development in both LMIC and UK settings.

## Ethics Statement

The studies involving human participants were reviewed and approved. Ethical approval has been granted from the Queen's University Belfast, School of Medicine, Dentistry and Biomedical Sciences ethics committee (reference number 18.43; v3 Sept 2018), and Research committee of the Universidad de Los Andes, Bogotá (937 - July 30, 2018). Written informed consent to participate in this study was provided by the participants' legal guardian/next of kin.
